### Immune status

Postoperative infections represent a major part of all complications within the first period after surgery(33-35). During and after major surgery hyperinflammatory responses, initiated by cytokine production, are accompanied and/or followed by counterregulatory anti-inflammatory responses. This can cause a dysfunctional state in which immune cells are unable to adequately respond to pathogens. This phenomenon, called surgery- or trauma- induced immunoparalysis, is associated with increased susceptibility to infectious complications after surgery, along with an increased mortality rate(36, 37).

As showed in the figure below, it is hypothesized that improving physical fitness by prehabilitation 1) improves the preoperative immune status and therefore 2) reduces the degree of immunoparalysis during and after major surgery. This might lead to less infectious complications after high impact surgery. Measuring the degree of immunoparalysis prior to prehabilitation, during and after high impact surgical procedures might give insight into the mechanistical effect of prehabilitation.

[figure not shown]

## 2. OBJECTIVES

Primary Objective: To determine the effects of a multimodal intensive prehabilitation program a high-risk patient group on complications (Clavien Dindo score and Comprehensive Complication Index (CCI) score)

Secondary Objective(s): To investigate the effects of multimodal intensive personalized prehabilitation on an:

- Individual patient's level, i.e. length of hospital stay (in days), physical fitness (estimated  $VO_2$  peak, indirect 1 repetition measures, physical activity), nutritional status (body weight, fat-free mass, Patient-Generated Subjective Global Assessment (PG-SGA), mental health (HRQoL), intervention adherence
- Mechanistic level, i.e. innate immune response (degree of immunoparalysis)
- Hospital-efficiency level: costs due to complications, costs due to length of hospital stay, budget impact, cost-effectiveness
- Macro-economic level: changes in patients volumes, shifts in care between 2nd and 1st line healthcare

### 3. STUDY DESIGN

This is a monocenter stepped-wedge cluster randomized trial of patients aged >16 years undergoing elective high impact surgery in Radboudumc, Nijmegen. Patients will be grouped into 20 clusters based on diagnosis; colon cancer, rectal cancer, esophageal cancer, liver metastases from colorectal cancer, pancreato-biliary cancer, peritoneal carcinomatosis from colorectal cancer, abdominal aortic aneurysm (open and endovascular), renal cancer, bladder cancer, supratentorial meningioma, hip arthrosis, osteosarcoma, pulmonary cancer, thoracic aortic aneurysm, head and neck cancer, mouth cancer, breast reconstruction, ovarian cancer or endometriosis. The prehabilitation program intervention will commence in one cluster each month with the order of clusters determined by computer based randomization. The stepped-wedge design allow delivery of the intervention at an organizational level with evaluation of outcome measures at a patients level. Structuring the prehabilitation program intervention through a staged activation in a random order provides important methodological advantages. The design allows to control adoption bias and to adjust for time-based changes in the background level of patient care in statistical analysis. A key strength of stepped-wedge design is that the prehabilitation program can be offered to every patient who is undergoing elective high impact surgery in Radboudumc, Nijmegen.

This stepped-wedge cluster randomized trial will be combined with an observational cohort study performed in Radboudumc on surgery induced danger-associated molecule patterns (DAMPs) and innate immune changes in patients undergoing endovascular aneurysm repair(38). Patients within the care path 'abdominal aortic aneurysm' will undergo additional blood tests, according to protocol, to determine the effect of prehabilitation on the innate immune response (see also 8. METHODS).

| Cluster | Pre
(24 months) |     |     |   | Switching (20 months) |   |   |   |   |   |   |   |   |   |   |   |   |   |   |   |   |   |   |   |   |   | Post
(4 months) |   |   |  |
|---------|--------------------|-----|-----|---|-----------------------|---|---|---|---|---|---|---|---|---|---|---|---|---|---|---|---|---|---|---|---|---|--------------------|---|---|--|
| 1       | 0                  | ... | ... | 0 | 1                     | 1 | 1 | 1 | 1 | 1 | 1 | 1 | 1 | 1 | 1 | 1 | 1 | 1 | 1 | 1 | 1 | 1 | 1 | 1 | 1 | 1 | 1                  | 1 | 1 |  |
| 2       | 0                  | ... | ... | 0 | 0                     | 1 | 1 | 1 | 1 | 1 | 1 | 1 | 1 | 1 | 1 | 1 | 1 | 1 | 1 | 1 | 1 | 1 | 1 | 1 | 1 | 1 | 1                  | 1 | 1 |  |
| 3       | 0                  | ... | ... | 0 | 0                     | 0 | 1 | 1 | 1 | 1 | 1 | 1 | 1 | 1 | 1 | 1 | 1 | 1 | 1 | 1 | 1 | 1 | 1 | 1 | 1 | 1 | 1                  | 1 | 1 |  |
| 4       | 0                  | ... | ... | 0 | 0                     | 0 | 0 | 1 | 1 | 1 | 1 | 1 | 1 | 1 | 1 | 1 | 1 | 1 | 1 | 1 | 1 | 1 | 1 | 1 | 1 | 1 | 1                  | 1 | 1 |  |
| 5       | 0                  | ... | ... | 0 | 0                     | 0 | 0 | 0 | 1 | 1 | 1 | 1 | 1 | 1 | 1 | 1 | 1 | 1 | 1 | 1 | 1 | 1 | 1 | 1 | 1 | 1 | 1                  | 1 | 1 |  |
| 6       | 0                  | ... | ... | 0 | 0                     | 0 | 0 | 0 | 0 | 1 | 1 | 1 | 1 | 1 | 1 | 1 | 1 | 1 | 1 | 1 | 1 | 1 | 1 | 1 | 1 | 1 | 1                  | 1 | 1 |  |
| 7       | 0                  | ... | ... | 0 | 0                     | 0 | 0 | 0 | 0 | 0 | 1 | 1 | 1 | 1 | 1 | 1 | 1 | 1 | 1 | 1 | 1 | 1 | 1 | 1 | 1 | 1 | 1                  | 1 | 1 |  |
| 8       | 0                  | ... | ... | 0 | 0                     | 0 | 0 | 0 | 0 | 0 | 0 | 1 | 1 | 1 | 1 | 1 | 1 | 1 | 1 | 1 | 1 | 1 | 1 | 1 | 1 | 1 | 1                  | 1 | 1 |  |
| 9       | 0                  | ... | ... | 0 | 0                     | 0 | 0 | 0 | 0 | 0 | 0 | 0 | 1 | 1 | 1 | 1 | 1 | 1 | 1 | 1 | 1 | 1 | 1 | 1 | 1 | 1 | 1                  | 1 | 1 |  |
| 10      | 0                  | ... | ... | 0 | 0                     | 0 | 0 | 0 | 0 | 0 | 0 | 0 | 0 | 1 | 1 | 1 | 1 | 1 | 1 | 1 | 1 | 1 | 1 | 1 | 1 | 1 | 1                  | 1 | 1 |  |
| 11      | 0                  | ... | ... | 0 | 0                     | 0 | 0 | 0 | 0 | 0 | 0 | 0 | 0 | 0 | 1 | 1 | 1 | 1 | 1 | 1 | 1 | 1 | 1 | 1 | 1 | 1 | 1                  | 1 | 1 |  |
| 12      | 0                  | ... | ... | 0 | 0                     | 0 | 0 | 0 | 0 | 0 | 0 | 0 | 0 | 0 | 0 | 1 | 1 | 1 | 1 | 1 | 1 | 1 | 1 | 1 | 1 | 1 | 1                  | 1 | 1 |  |
| 13      | 0                  | ... | ... | 0 | 0                     | 0 | 0 | 0 | 0 | 0 | 0 | 0 | 0 | 0 | 0 | 0 | 1 | 1 | 1 | 1 | 1 | 1 | 1 | 1 | 1 | 1 | 1                  | 1 | 1 |  |
| 14      | 0                  | ... | ... | 0 | 0                     | 0 | 0 | 0 | 0 | 0 | 0 | 0 | 0 | 0 | 0 | 0 | 0 | 1 | 1 | 1 | 1 | 1 | 1 | 1 | 1 | 1 | 1                  | 1 | 1 |  |
| 15      | 0                  | ... | ... | 0 | 0                     | 0 | 0 | 0 | 0 | 0 | 0 | 0 | 0 | 0 | 0 | 0 | 0 | 0 | 1 | 1 | 1 | 1 | 1 | 1 | 1 | 1 | 1                  | 1 | 1 |  |
| 16      | 0                  | ... | ... | 0 | 0                     | 0 | 0 | 0 | 0 | 0 | 0 | 0 | 0 | 0 | 0 | 0 | 0 | 0 | 0 | 1 | 1 | 1 | 1 | 1 | 1 | 1 | 1                  | 1 | 1 |  |
| 17      | 0                  | ... | ... | 0 | 0                     | 0 | 0 | 0 | 0 | 0 | 0 | 0 | 0 | 0 | 0 | 0 | 0 | 0 | 0 | 0 | 1 | 1 | 1 | 1 | 1 | 1 | 1                  | 1 | 1 |  |
| 18      | 0                  | ... | ... | 0 | 0                     | 0 | 0 | 0 | 0 | 0 | 0 | 0 | 0 | 0 | 0 | 0 | 0 | 0 | 0 | 0 | 0 | 1 | 1 | 1 | 1 | 1 | 1                  | 1 | 1 |  |
| 19      | 0                  | ... | ... | 0 | 0                     | 0 | 0 | 0 | 0 | 0 | 0 | 0 | 0 | 0 | 0 | 0 | 0 | 0 | 0 | 0 | 0 | 0 | 1 | 1 | 1 | 1 | 1                  | 1 | 1 |  |
| 20      | 0                  | ... | ... | 0 | 0                     | 0 | 0 | 0 | 0 | 0 | 0 | 0 | 0 | 0 | 0 | 0 | 0 | 0 | 0 | 0 | 0 | 0 | 0 | 0 | 1 | 1 | 1                  | 1 | 1 |  |

Retrospectively, 24 months of pre-measurements will be collected. The prospective data collection will include 20 months in which every month one cluster switches and 4 months of post-measurements. In the above a '0' indicates the control condition and a '1' the intervention condition.

## 4. STUDY POPULATION

### 4.1 Population (base)

Patients undergoing 20 types of elective high impact surgical procedures, as shown in the table below, in Radboudumc will be included in this study.

Table 1. Type of surgical procedure per diagnosis

| Diagnosis                                        | Surgical procedure                     |
|--------------------------------------------------|----------------------------------------|
| Colon cancer                                     | Colon resection                        |
| Rectal cancer                                    | Rectal resection                       |
| Esophageal cancer                                | Esophageal resection                   |
| Liver metastases from colorectal cancer          | Liver resection                        |
| Pancreato-biliary cancer                         | Pancreas resection                     |
| Peritoneal carcinomatosis from colorectal cancer | HIPEC                                  |
| Abdominal aortic aneurysm (open)                 | Open abdominal aortic aneurysm repair  |
| Abdominal aortic aneurysm (endovascular)         | EVAR                                   |
| Renal cancer                                     | Nephrectomy                            |
| Bladder cancer                                   | Cystectomy                             |
| Supratentorial meningioma                        | Craniotomy                             |
| Hip arthrosis                                    | Total hip arthroplasty                 |
| Osteosarcoma                                     | Limb salvage procedure                 |
| Pulmonary cancer                                 | Lung resection                         |
| Thoracic aortic aneurysm                         | Open thoracic aortic aneurysm repair   |
| Head and neck cancer                             | Laryngectomy                           |
| Mouth cancer                                     | Mandibular resection or reconstruction |
| Breast reconstruction                            | DIEP flap reconstruction               |
| Ovarian cancer                                   | Hysterectomy                           |
| Endometriosis                                    | Excision of endometriosis              |

### 4.2 Inclusion criteria

In order to be eligible to participate in this study, a subject must meet all of the following criteria:

- Patients >16 years,
- scheduled for elective high impact surgery,
- independent of (neo-) chemotherapy and/or radiotherapy,
- obtained written informed consent.

### **4.3 Exclusion criteria**

A potential subject who meets any of the following criteria will be excluded from participation in this study:

- Metastatic disease known preoperatively (exemption colorectal carcinoma liver metastases and peritoneal carcinomatosis from colorectal or ovarian cancer),
- paralytic or immobilized patients who are not able to complete exercise intervention,
- premorbid conditions or orthopedic impairments which contraindicate exercise,
- cognitive disabilities,
- unstable cardiac or respiratory disease,
- renal failure stage 3 or higher,
- ASA score 4 or higher,
- illiteracy (disability to read and understand Dutch).

A patient accrual rate of 60-80 percent is estimated.

[figure not shown]

#### 4.4 Sample size calculation

We consulted [name], department of Epidemiology, Radboudumc for the sample size calculation.

The calculation for this stepped-wedge cluster randomized trial is based on 20% relative reduction in the percentage of Clavien-Dindo score II or higher.

Table 2. Numbers of surgical procedures/year and overall complication rates in Radboudumc

| Surgical procedure                     | Numbers of surgical procedures/year | Overall complication rates (Clavien-Dindo II or higher) |
|----------------------------------------|-------------------------------------|---------------------------------------------------------|
| Colon resection                        | 65                                  | 15%                                                     |
| Rectal resection                       | 60                                  | 15%                                                     |
| Esophageal resection                   | 80                                  | 55%                                                     |
| Liver resection                        | 100                                 | 15%                                                     |
| Pancreas resection                     | 78                                  | 33%                                                     |
| HIPEC                                  | 40                                  | 30%                                                     |
| Open abdominal aortic aneurysm repair  | 35                                  | 58%                                                     |
| EVAR                                   | 120                                 | 24%                                                     |
| Nephrectomy                            | 60                                  | 25%                                                     |
| Cystectomy                             | 78                                  | 38%                                                     |
| Craniotomy                             | 55                                  | 11%                                                     |
| Total hip arthroplasty                 | 50                                  | 10% (based on literature)                               |
| Limb salvage procedure                 | 30                                  | 30% (based on literature)                               |
| Lung resection                         | 60                                  | 20% (based on literature)                               |
| Open thoracic aortic aneurysm repair   | 150                                 | 10% (based on literature)                               |
| Laryngectomy                           | 65                                  | 30% (based on literature)                               |
| Mandibular resection or reconstruction | 60                                  | 35% (based in literature)                               |
| DIEP flap reconstruction               | 118                                 | 22%                                                     |
| Hysterectomy                           | 50                                  | 10% (based on literature)                               |
| Excision of endometriosis              | 50                                  | 30% (based on literature)                               |

Sample size was based on simulations in a log-binomial model with cluster (surgical procedure), intervention, and time (as continuous variable) as fixed effects. Monthly binary data were generated per cluster (surgical procedure) per month with a binary distribution according to the sample size corresponding to Table 2 with a small overall time trend. The percentage complications in the control condition was based on Table 2, and in the intervention condition this percentage had a relative reduction of 20% (e.g., nephrectomy was assumed to change from 25% to 20%). Based on the simulations, power was 83%.

Based on actual recruitment, the number of retrospectively pre-measurements and prospectively collected post-measurements may be increased (see 10.4). The total prospective recruitment in terms of patients is expected to be 2828 (2 year times 1414 patients/year), although the power will not primarily be driven by the total number of patients but rather their distribution over clusters over time.

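### The 2828 prospective patients and the 83% power in Section 4.4 rest on full procedure volume, although Section 4.3 estimates 60-80% accrual; neither figure carries an accrual factor

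*Protocol*

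**What the plan says.** Section 4.4 takes its effect size from the binary complication outcome: the calculation is "based on 20% relative reduction in the percentage of Clavien-Dindo score II or higher". Table 2 lists 20 procedures, and its size column is headed "Numbers of surgical procedures/year". Monthly data were simulated "according to the sample size corresponding to Table 2 with a small overall time trend", and "The percentage complications in the control condition was based on Table 2". The model is log-binomial with cluster, intervention and continuous time as fixed effects. The result: "Based on the simulations, power was 83"%. On recruitment: "The total prospective recruitment in terms of patients is expected to be 2828 (2 year times 1414 patients/year").

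Section 4.3 closes the eligibility criteria with: "A patient accrual rate of 60-80 percent is estimated". Section 4.2 makes written informed consent an inclusion criterion, and Section 4.3 lists eight exclusions.

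Sections 4.4 and 10.4 allow more retrospective and more post-switch data to be collected if clusters recruit fewer than expected, after a blinded look at recruitment.

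**The concern.** Table 2 counts operations performed, not patients enrolled. Section 4.4 carries those counts unreduced into both the simulation and the expected recruitment, so it takes accrual as 100%. Section 4.3 expects 60-80%. The protocol cannot hold both expectations.

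The stated power is what an ethics committee or a later reader will use to interpret a non-significant result. If the trial recruits exactly as Section 4.3 predicts, it has fewer patients in every prospective cell than the 83% was computed for. The extension clause depends on recruitment below expectation, and the recruitment expected in Section 4.4 is itself set at full volume.

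**Working it through.** **Recruitment.** The Table 2 rows, in order:

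65 + 60 + 80 + 100 + 78 + 40 + 35 + 120 + 60 + 78 + 55 + 50 + 30 + 60 + 150 + 65 + 60 + 118 + 50 + 50 = 1404 per year.

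- Two years: 2 × 1404 = 2808, against the stated 2 × 1414 = 2828. The gap of 20 is 0.7%, so 2828 is full volume apart from a slip in the sum.
- At 60%: 0.6 × 2808 = 1685. At 80%: 0.8 × 2808 = 2246. (With 1414 per year: 1697 and 2262.)

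**Power inputs from the protocol.** Table 2 sizes divided by 12 per month; Table 2 control rates; risk ratio 0.80; 24 retrospective months, 20 monthly switches and 4 further months (Section 3); log-binomial model with 20 cluster effects, intervention and linear time.

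**Power inputs assumed, because Section 4.4 does not give them.** Alpha 0.05 two-sided; size, direction and starting point of the time trend.

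**Formula.** For each cluster-month with m patients and complication probability p, the log-binomial information weight is m·p/(1 − p). Summing these over the design matrix and inverting gives the standard error (SE) of the log risk ratio. Then power = Φ(−ln 0.80 / SE − 1.96), with −ln 0.80 = 0.2231, averaged over random switching orders.

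**The plan's own figure.** At full volume without a trend, the SE is 0.0818: 0.2231/0.0818 − 1.96 = 0.77, power 78% (simulated trials: 77%). Other unstated choices move this result:

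- A rise of about 3.5% per year in the complication rate, with Table 2 rates holding at month 0, gives SE 0.0766 and 83%.
- The same rise with Table 2 rates holding at the start of switching gives 79%.
- A fall of 2% per year from month 0 gives 75%.
- A one-sided 5% test without a trend gives 86%.

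So 83% is reachable, but not from the stated inputs alone.

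**Effect of accrual (two-sided 5%), each column against its own full-volume value.**

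| Accrual | No trend: prospective months only | No trend: both periods | +3.5%/year from month 0: prospective months only | +3.5%/year: both periods |
|---|---|---|---|---|
| 100% | 78% | 78% | 83% | 83% |
| 80% | 71% | 68% | 76% | 74% |
| 70% | 67% | 63% | 72% | 68% |
| 60% | 62% | 56% | 67.5% | 62% |

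For example, at 80% accrual in the prospective months without a trend, SE = 0.0888 and 0.2231/0.0888 − 1.96 = 0.55, power 71%. At 60%, SE = 0.0986 and 0.2231/0.0986 − 1.96 = 0.30, power 62%. Every entry at 60-80% accrual is below 80%.

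**Effect of the extension (no trend, retrospective data complete).** Twelve more retrospective months (36 + 20 + 4) give 81% at 80% accrual and 73% at 60%. Six more post-switch months alone add about 1 point.

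**The case against.** Four arguments can be made for the text as it stands.

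First, the simulation included a time trend whose size is not reported, and alpha is not reported either. A reader might infer from the 78% that the stated 83% is wrong. The protocol does not support that: a modest rising trend from month 0 returns 83%. For the same reason it would be wrong to set 62-71% beside 83% as the loss due to accrual, because the two come from different baselines. This objection stands. It limits the finding to like-for-like losses, and it means the replacement power must come from the sponsor's own simulation.

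Second, the protocol provides a remedy: more retrospective and post-switch data if clusters fall short. This has real force. Besides the 36-month figures above, 48 retrospective months without a trend would give about 87% at 80% accrual and 79% at 60%. But the provision is permissive and names no amount or trigger. The stated 83% also does not depend on it, so it does not reconcile Sections 4.3 and 4.4.

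Third, Section 4.4 says that power depends more on how patients are spread over clusters and time than on their total. The calculation respects that spread. Thinning every prospective cell to 80% or 60% still costs 7 to 16 points without a trend (78% to 71% or 62%).

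Fourth, the accrual sentence does not say whether its base is operated, eligible or approached patients, and the figure beside it is not available in the text reviewed. This stands as a condition on the 1685-2246 range. The requirement for consent and the eight exclusions make accrual of every operated patient implausible on any of these bases.

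**Conclusion.** The inconsistency holds: expected recruitment and simulated power use 100% of procedures, while the protocol estimates 60-80% accrual. If that rate applies to operated patients, prospective recruitment is about 1685-2246, which is 20-40% below full volume.

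With two-sided 5% and accrual reduced in the prospective months only, power falls from 78% to about 62-71% without a trend, or from 83% to about 67-76% under a trend that returns 83%. If the retrospective data shrink equally, the ranges are about 56-68% and 62-74%. All are below 80% unless the periods are extended.

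A reader might go further and conclude that the stated 83% is an error, or that the trial's true power is about two in three. The protocol supports neither, because alpha, sidedness and trend are undisclosed and an extension is possible. The 1404 against 1414 discrepancy is a slip with negligible effect on power.

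**What to change.** In Section 4.4:

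- Correct 1414 to 1404.
- Replace 2828 with the accrual-adjusted range (about 1685-2246 if the base is operated patients), and state in Section 4.3 what the 60-80% is a percentage of.
- Rerun the existing simulation with prospective cell sizes multiplied by 0.6, 0.7 and 0.8. State alpha, sidedness, the size and starting point of the time trend, and whether the retrospective cells are also reduced.
- Replace the 83% with the powers from that rerun.
- State here and in Section 10.4 how many months the retrospective and post-switch periods would be extended if accrual lies in that range, and what would trigger it.

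The cost is a rerun of existing code and a few reworded sentences. No extra enrolment is requested. The only downside is that the stated power will probably look less favourable.
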